#### Neonatal management and follow-up

Neonatal management will be exactly the same as it would be in routine practice. Infants will be followed from birth to discharge home or until a maximum of 24 weeks of age, whichever comes first.

#### Child follow-up

We will perform a follow-up at 2 years of corrected age, with a self-administered questionnaire sent to the parents, by email and/or postal mail, by using the contact details they provided at inclusion. Besides severe morbidity considered as a secondary endpoint, we will evaluate the children’s growth, health, neurodevelopment, and living conditions (family situation and socioeconomic conditions). Another follow-up evaluation at the age of 5 years is under consideration, if additional funding can be obtained.

#### Duration of the trial

The total duration of the trial will be 71 months, including 42 months of inclusions and the follow-up at 2 years of corrected age (i.e., for a maximum of 29 months for infants born extremely preterm).

### Outcome measures

#### Primary outcome measure

The primary endpoint is a composite outcome of perinatal mortality/morbidity until hospital discharge (or up to a maximum of 24 wks after birth if the infant is still hospitalized). It includes fetal death (in utero fetal death occurring from randomization to birth), neonatal death (death from birth to discharge, in the delivery room or neonatal intensive care unit [NICU]), and/or severe neonatal morbidity [51] defined as any one or more of the following:
Mechanical ventilation ≥48 h, defined as high frequency or conventional mechanical ventilation for at least 48 consecutive hours during hospitalization [52];Severe bronchopulmonary dysplasia (BPD), defined as requiring oxygen for at least 28 days plus the need for 30% or more oxygen and/or mechanical ventilator support or continuous positive airway pressure at 56 days postnatal age or 36 weeks’ postmenstrual age or discharge, whichever comes first [53];Severe intraventricular hemorrhage (IVH), defined as IVH associated with ventricular dilatation (grade III IVH) and intraparenchymal hemorrhage (i.e., large unilateral parenchymal hyperdensity or large unilateral porencephalic cyst, grade IV IVH); diagnosed by ultrasound [54];Cystic periventricular leukomalacia, defined as periventricular white matter echolucencies on ultrasonography [55];Early-onset sepsis, diagnosed from positive bacteriology findings in blood or cerebrospinal fluid (confirmed infection) that began in the first 3 days of life [56];Necrotizing enterocolitis, stages II and III according to Bell’s staging [57];Retinopathy of prematurity, stage 3 or greater according to the international classification [58] and/or laser treatment.

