### Inclusion criteria

Pregnant women are eligible for the trial if they meet all of the following criteria:
PPROM, diagnosed by obstetric teams, between 22^0/7^ and 33^6/7^ weeks of gestation, dated according to the first-trimester ultrasonography.Singleton pregnancy.Fetus alive at randomization.Age ≥ 18 years.Speaks French.Affiliated with the French national health insurance or an equivalent system.Provided written informed consent.

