#### Secondary outcome measures

Prolongation of gestation will be evaluated by various different criteria:
Latency duration, defined as the interval from PPROM to delivery.Pregnancy prolongation beyond 48 h after randomization,Pregnancy prolongation beyond 1 week after randomization,Gestational age at delivery,Delivery after 37 weeks of gestation.

Maternal morbidity will be assessed by clinical diagnosis of intrauterine infection, defined as fever (maternal temperature ≥ 38 °C), with no alternative cause identified, associated with at least two of the following criteria: persistent fetal tachycardia > 160 bpm, uterine pain or painful uterine contractions or spontaneous labor, purulent amniotic fluid [21]; and endometritis, based on the association of fever (temperature ≥ 38.0 °C) with uterine tenderness, purulent or foul-smelling lochia, and in the absence of any other cause, during the first 10 days after delivery [59].

For neonatal morbidity, we will isolate each criterion included in the composite primary outcome and assess its association with the intervention. We will also study:
Severe fetal acidemia, defined as cord umbilical artery pH less than 7.00 or base deficit greater than 16 mEq/L (16 mmol/L), or both [60];Respiratory distress syndrome, defined from clinical diagnosis as the presence of clinical signs of respiratory distress (tachypnea, retractions, flaring, grunting, or cyanosis), with a requirement for supplemental oxygen with a fraction of inspired oxygen more than 0.21 and a chest radiograph showing hypoaeration and reticulogranular infiltrates;Mild or moderate BPD, defined as requiring oxygen for at least 28 days plus the need for 21% (mild) - 30% (moderate) oxygen at 56 days postnatal age or 36 weeks’ postmenstrual age or discharge, whichever comes first [53];Grades I-II IVH, defined according to Papile’s classification: subependymal hemorrhage (grade I IVH) or IVH without ventricular dilatation (grade II IVH), diagnosed by ultrasound [54];Late-onset sepsis, diagnosed from positive bacteriology findings in blood or cerebrospinal fluid (confirmed infection) that began after 72 h of life [61].

At 2 years of corrected age, we will evaluate the following criteria [51]:

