### Statistical issues

#### Sample size

Within the prospective, national, population-based EPIPAGE-2 cohort study of preterm births, we selected a sample of 888 women according to the TOCOPROM eligibility criteria and estimated the frequency of infants diagnosed with any criterion of the composite primary outcome to be 35.5%. This is an average estimate taking into account the expected variation of gestational age at birth in our study population from 22 to 37+ weeks. This estimate is consistent with findings in recent studies [15, 52, 66].

We hypothesized that the beneficial effect of tocolysis would be mediated by both higher gestational age at birth and the administration of a complete course of antenatal corticosteroids. The EPIPAGE-2 study showed that among women with PPROM, each one-day increase in gestational age at birth is significantly associated with a reduced relative risk (RR) of fetal or neonatal death or severe morbidity (RR 0.95, 95% CI 0.91–0.99) [10]. With pregnancy prolonged by 48 h by effective tocolysis, we expect to reduce the rate of fetal or neonatal death or severe morbidity by 10%. Each additional day after the initial 48-h period will also contribute to reducing adverse outcomes. Moreover, this initial prolongation will allow a complete course of antenatal corticosteroids, with additional beneficial effects, as shown by Roberts et al. [28, 67]. In meta-analyses of women with PPROM, antenatal steroids have been associated with reduced perinatal (RR 0.59, 95%CI 0.39–0.90) and neonatal mortality (RR 0.61, 0.46-0.83), respiratory distress syndrome (RR 0.70, 0.55-0.90), chronic lung disease (RR 0.50, 0.33–0.76), necrotizing enterocolitis (RR 0.39, 0.18–0.86), and IVH (RR 0.47, 0.28-0.79). Retinopathy of prematurity, early-onset sepsis, and periventricular leukomalacia were not analyzed separately by membrane status in these meta-analyses.

When we assume an alpha-risk of 0.05 and a beta-risk of 0.20 (i.e., statistical power of 80%), 702 women (351 per arm) are required to show a reduction of the primary endpoint from 35% (placebo group) to 25% (nifedipine group). We plan to increase the required number of subjects by 20%, to replace patients who leave the study early. The total number of subjects required is thus 850.

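### The BPD timing rule, part of the primary endpoint, is not tied to gestational age at birth and cannot be applied consistently across the births the trial expects

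*Protocol article*

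**What the plan says.** Under Primary outcome measure, the protocol article defines severe BPD by two conditions. The first and the type of support are given as "requiring oxygen for at least 28 days plus the need for 30% or more oxygen and/or mechanical ventilator support or continuous positive airway pressure". The time at which that support is judged is "56 days postnatal age or 36 weeks’ postmenstrual age or discharge, whichever comes first".

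Under Secondary outcome measures, mild and moderate BPD also require 28 days of oxygen and use the same timing: "oxygen at 56 days postnatal age or 36 weeks’ postmenstrual age or discharge, whichever comes first".

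Neither definition links a time point to gestational age at birth. Two other statements matter here:

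- Sample size describes the planning rate as covering the "expected variation of gestational age at birth in our study population from 22 to 37+ weeks", so one rule has to serve that whole range.
- Sample size also states the hypothesis that "the beneficial effect of tocolysis would be mediated by both higher gestational age at birth", together with completed antenatal steroids.

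**The concern.** Day 56 and 36 weeks' postmenstrual age (PMA) are different kinds of landmark. One is counted from birth and the other from conception dating, so which comes first depends only on how early the infant was born. Taking the earliest for every infant makes the assessment time a function of gestational age at birth. In part of the expected range it also sets the assessment ahead of the definition's own 28-day condition, and for the latest births it gives no meaningful date.

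Two things are at stake. First, a component of the primary endpoint must be derivable in the same way for every infant in 29 centres. If the literal rule fails, abstractors will fill the gap case by case. Second, the assessment time depends on a post-randomisation variable that treatment is intended to shift. Each component is also to be analysed separately, so the BPD result will stand on its own as well as inside the composite.

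**Working it through.** The plan gives no figure to reproduce here; the check is date arithmetic.

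**Inputs**
- Time points: day 56, 36 weeks' PMA (36 × 7 = 252 days) and discharge, earliest applies (Primary and Secondary outcome measures).
- Oxygen condition: at least 28 days (same sections).
- Births expected from 22 to 37+ weeks (Sample size).
- Neonatal follow-up to discharge or 24 weeks of age, i.e. 24 × 7 = 168 days (Neonatal management and follow-up).

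**Formulas.** Let g be gestational age at birth in days, with the day of birth as day 0.
- 36 weeks' PMA is reached on day 252 − g.
- Assessment day = min(56, 252 − g), or discharge if earlier.
- PMA at assessment = g + assessment day.

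**Results**, for infants still in hospital:

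| Birth | g | Day of 36 weeks' PMA | Assessment day | PMA at assessment | Days before 36 weeks' PMA | 28 days elapsed? |
|---|---|---|---|---|---|---|
| 22+0 | 154 | 98 | 56 | 30+0 | 42 | yes |
| 24+0 | 168 | 84 | 56 | 32+0 | 28 | yes |
| 26+0 | 182 | 70 | 56 | 34+0 | 14 | yes |
| 27+6 | 195 | 57 | 56 | 35+6 | 1 | yes |
| 28+0 | 196 | 56 | 56 | 36+0 | 0 | yes |
| 30+0 | 210 | 42 | 42 | 36+0 | 0 | yes |
| 32+0 | 224 | 28 | 28 | 36+0 | 0 | just |
| 32+1 | 225 | 27 | 27 | 36+0 | 0 | no |
| 33+0 | 231 | 21 | 21 | 36+0 | 0 | no |
| 33+6 | 237 | 15 | 15 | 36+0 | 0 | no |
| 35+0 | 245 | 7 | 7 | 36+0 | 0 | no |
| 36+0 | 252 | 0 | 0 | none usable | – | no |

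**Reading the table**
1. 252 − g > 56 whenever g < 196. Before 28+0, day 56 always comes first and 36 weeks' PMA never applies.
2. 252 − g < 28 whenever g > 224. After 32+0, assessment precedes the point at which 28 days of oxygen could have elapsed.
3. 252 − g ≤ 0 whenever g ≥ 252. From 36+0, 36 weeks' PMA falls on or before the day of birth, so the earliest-date rule has nothing to select.

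**Dependence on gestational age at birth.** Before 28+0, one day gained leaves the postnatal age at assessment unchanged and moves it one day later in PMA. From 28+0 up to 36 weeks, one day gained leaves PMA unchanged and moves assessment one postnatal day earlier. A 48 h gain therefore moves the assessment by at most two days on one scale or the other.

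**Observability.** The latest date that either landmark could require is day 98 (birth at 22+0, 36 weeks' PMA), well inside the 168-day limit. A rule split by gestational age needs no longer follow-up.

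**The case against.** Several stronger conclusions are tempting, and the case against them is good.

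- **BPD is unattainable from 32 weeks.** A reader might infer this, but it is wrong at 32+0, where day 28 and 36 weeks' PMA coincide. After 32+0 it holds only if the 28 oxygen days must be complete at assessment. The text merely joins the two conditions. An infant born at 33+0 who needs 30% oxygen on day 21 and remains on oxygen to day 28 satisfies both on the looser reading. The same infant fails on the stricter one, which is an ambiguity to settle.
- **Infants below 28 weeks are judged too early, or over-called.** This needs a reference standard. The article shows only that day 56 precedes 36 weeks' PMA; the definition it cites, reference [53], is not at hand. CPAP at day 56 is also not enough alone, because 28 days of oxygen are required too.
- **The timing rule favours the treated arm.** Any landmark moves with gestational age at birth on one scale or the other. A 36-week landmark would fix PMA but let postnatal age vary (day 98 at 22+0, day 84 at 24+0). Less need for support after a later birth is also the hypothesised benefit, so it cannot simply be called an artefact.
- **The composite is materially affected.** Severe BPD is one of seven morbidities alongside fetal and neonatal death. Some affected infants will already count through death or ventilation of at least 48 h. The article gives no BPD rate, overlap or distribution of gestational age at birth.

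It can also be said that neonatal data come from hospital reports, which the Data collection section describes as generally standardised to international definitions, and that the article condenses a fuller protocol. That makes the actual derivation unknown. It does not cure the text, because the article states an operative rule twice and leaves abstractors to choose between it and the recorded diagnosis.

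**Conclusion.** The point stands as a defect of definition and should be fixed; the documents do not support treating it as a demonstrated bias. As written, the rule assesses births before 28+0 at day 56, 1 to 42 days ahead of 36 weeks' PMA. It assesses births after 32+0 before the 28-day condition can have been met, and it gives no usable date from 36+0. All three ranges lie within the births the protocol expects.

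The calculation assumes that the rule is applied literally, that the infant is still in hospital, and that the day of birth is day 0. The first two turning points move by one day if birth is counted as day 1. Neither the direction nor the size of any effect on the relative risk, or on the 35% and 25% planning rates, can be derived from the article. Whether the 35.5% estimate from the EPIPAGE-2 cohort used the same BPD rule is also not stated.

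**What to change.** Before database lock and unblinding:

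1. Tie each time point to gestational age at birth, in identical terms under Primary and Secondary outcome measures. A split consistent with the protocol's own 28-day condition is 36 weeks' PMA (or discharge, if earlier) for births before 32 weeks, and day 56 (or discharge, if earlier) for births from 32 weeks. Check it against the cited definition [53] before adopting it.
2. State whether the 28 days of oxygen must be complete at assessment.
3. Derive the component in the same way for all centres from dated respiratory support in the neonatal record, rather than accepting a recorded diagnosis in some and the literal rule in others.
4. Check that the 35.5% planning rate was obtained with the same rule, and report any difference.

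The split has a drawback: assessment jumps from day 29 (birth at 31+6) to day 56 (birth at 32+0), at a cut-point that is itself post-randomisation. It does not remove the dependence on gestational age at birth, but it gives every expected birth a usable date that is compatible with the 28-day condition.

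The cost is revised wording, one programmed derivation, a record check for infants already entered, and possibly one extra dated field on the e-CRF. Follow-up need not be extended. With no interim analysis planned and the statistician blinded, the change can be made without knowledge of results by arm.

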#### Secondary outcome measures

Prolongation of gestation will be evaluated by various different criteria:
Latency duration, defined as the interval from PPROM to delivery.Pregnancy prolongation beyond 48 h after randomization,Pregnancy prolongation beyond 1 week after randomization,Gestational age at delivery,Delivery after 37 weeks of gestation.

Maternal morbidity will be assessed by clinical diagnosis of intrauterine infection, defined as fever (maternal temperature ≥ 38 °C), with no alternative cause identified, associated with at least two of the following criteria: persistent fetal tachycardia > 160 bpm, uterine pain or painful uterine contractions or spontaneous labor, purulent amniotic fluid [21]; and endometritis, based on the association of fever (temperature ≥ 38.0 °C) with uterine tenderness, purulent or foul-smelling lochia, and in the absence of any other cause, during the first 10 days after delivery [59].

For neonatal morbidity, we will isolate each criterion included in the composite primary outcome and assess its association with the intervention. We will also study:
Severe fetal acidemia, defined as cord umbilical artery pH less than 7.00 or base deficit greater than 16 mEq/L (16 mmol/L), or both [60];Respiratory distress syndrome, defined from clinical diagnosis as the presence of clinical signs of respiratory distress (tachypnea, retractions, flaring, grunting, or cyanosis), with a requirement for supplemental oxygen with a fraction of inspired oxygen more than 0.21 and a chest radiograph showing hypoaeration and reticulogranular infiltrates;Mild or moderate BPD, defined as requiring oxygen for at least 28 days plus the need for 21% (mild) - 30% (moderate) oxygen at 56 days postnatal age or 36 weeks’ postmenstrual age or discharge, whichever comes first [53];Grades I-II IVH, defined according to Papile’s classification: subependymal hemorrhage (grade I IVH) or IVH without ventricular dilatation (grade II IVH), diagnosed by ultrasound [54];Late-onset sepsis, diagnosed from positive bacteriology findings in blood or cerebrospinal fluid (confirmed infection) that began after 72 h of life [61].

At 2 years of corrected age, we will evaluate the following criteria [51]:
Vital status (ascertainment of whether the child died between discharge and follow-up at 2 years or is still alive);Cerebral palsy, defined according to the diagnostic criteria of the Surveillance of Cerebral Palsy in Europe (SCPE) network [62], with severity graded with the five-level Gross Motor Function Classification System (GMFCS) [63];Hearing impairment, defined as deafness or functional hearing loss requiring correction and classified as severe (bilateral) or moderate (unilateral) [64];Visual impairment, defined as blindness or the ability to see light only, and classified as severe (bilateral) or moderate (unilateral) [64]. Squinting or the need for glasses will also be recorded;Neurodevelopment, assessed with the second version of the 24-month Ages and Stages Questionnaire (ASQ), which is validated in France and covers five developmental domains: communication abilities, gross motor skills, fine motor skills, problem-solving abilities, and personal-social skills [64, 65].

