## Background

### Rationale

#### Epidemiology of PPROM and neonatal consequences

Preterm prelabor rupture of membranes (PPROM) is defined as spontaneous rupture of the fetal membranes occurring before the onset of labor and before 37 weeks of gestation [1, 2]. PPROM is a complex and multifactorial pathology, resulting from the progressive weakening of the membranes under the effect of chemical, mechanical, and/or infectious factors [3]. This degeneration begins several weeks before manifesting clinically by the flow of amniotic fluid [4, 5]. Primary and secondary prevention of preterm birth are very challenging: although some risk factors have been identified, most women have none, and there are no validated predictive models and no effective preventive interventions [6, 7].

PPROM complicates 2–3% of pregnancies [1, 7]. Despite the rupture of membranes, pregnancy can be prolonged by a latency period (defined as the time elapsed from PPROM to delivery) ranging from a few hours to several weeks. About 50 to 60% of women will give birth within the first week after PPROM [8–10], which is thus responsible for a large share of preterm births (25 to 30%) [1, 11] and is a leading cause of neonatal mortality and morbidity and maternal infectious morbidity [7, 12]. Although the infant’s prognosis depends mainly on gestational age at birth [13–15], fetal exposure to inflammation, infection, and acute obstetric complications (placental abruption, umbilical cord compression or prolapse) can increase short- and long-term mortality/morbidity [16–18]. Consequently, in cases of PPROM, medical teams must weigh the benefits of prolonging pregnancy to reduce prematurity-related adverse consequences against those of inducing delivery to shorten exposure to intrauterine inflammation, infection, and acute obstetric complications.

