### Exclusion criteria

Pregnant women are not eligible for the trial if they meet any of the following criteria:
PPROM diagnosis ≥24 h after amniotic fluid leak.Ongoing tocolytic treatment at the time of PPROM.Tocolytic treatment with nifedipine between PPROM diagnosis and randomization (*before July 16, 2021, this criterion was “Any tocolytic treatment between PPROM diagnosis and randomization”. This modification was introduced after randomizing 211 patients and was intended to improve the potential for inclusion by making patients receiving a brief tocolysis during* in utero *transfer eligible.)*Fetal condition contraindicating expectant management (including intrauterine infection, placental abruption, hemorrhagic placenta previa, intrauterine fetal demise, non-reassuring fetal heart rate).Cervical dilation ≥5 cm.Iatrogenic rupture of membranes caused by amniocentesis or trophoblast biopsy.Major fetal anomaly.Maternal allergy or contraindication to nifedipine or placebo drug components (myocardial infarction, unstable angina pectoris, hepatic insufficiency, cardiovascular shock, beta blockers, and cardiopathy).Co-administration of diltiazem, rifampicin, transdermal nitrates, or any antihypertensive medication.Hypotension (systolic blood pressure < 90 mmHg).Participation in another interventional research study (Category 1).

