### Study procedures

#### Recruitment

Each woman presenting at a participating center with possible PPROM will be examined by a midwife or an obstetrician to confirm or rule out this diagnosis. PPROM diagnosis, according to national clinical guidelines, is usually based on 2 positive criteria from maternal history, sterile speculum examination to confirm fluid leakage from the cervical canal, and performance of a diagnostic test [21]. Women transferred from another center will be eligible if PPROM occurred within the previous 24 h and if they did not receive nifedipine after the PPROM diagnosis (women who received other tocolytics during in utero transfer, such as atosiban, which has a very short half-life, are eligible from July 16, 2021 onwards).

Eligible women who meet inclusion criteria will be identified by a local investigator (obstetrician or midwife) and informed about the trial (orally and with a written patient information form) (Table 2). Those who choose to participate, after a reflection period if necessary, will provide written informed consent. A second informed consent form, signed by the mother and father (at inclusion, delivery, or follow-up assessment), is required for the follow-up of children at 2 years of corrected age.

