#### Statistical analysis

Data analysis and reporting will follow the CONSORT guidelines for randomized controlled trials [68] and will be conducted according to the following principles. The trial statistician and researchers will be blinded to group status. No intermediate analysis is planned, as there is no added risk for women and neonates from this study compared with routine practices in France. Data will be analyzed by the intention-to-treat principle, i.e., all randomized participants will be analyzed according to their original allocation, regardless of protocol adherence. Baseline demographic and clinical characteristics of women, including adherence to the protocol, and outcomes will be described and compared by allocated treatment. Categorical variables will be summarized by numbers and percentages of patients in each treatment group and compared by Chi-2 or Fisher’s exact tests, as appropriate. Quantitative variables will be presented as means (standard deviations) if their distribution is normal and medians (interquartile ranges) otherwise; they will be compared with Student or Mann-Whitney-Wilcoxon tests, as appropriate. All these statistical tests will be two-sided and the level of statistical significance will be set at 5% (2-sided).

The effects of tocolysis will be expressed as relative risks with their 95% CIs for categorical outcomes and as mean differences with their 95% CIs for quantitative outcomes. Risk ratios and 95% CIs will be calculated for the primary outcome by using Poisson regression with a robust variance estimation, first unadjusted and then adjusted for minimization factors. Center will be fitted as a random effect, and the other minimization factors as fixed effects. The results will also be expressed as absolute risk differences with 95% CIs for binary outcomes. We will assess the Number Needed to Treat (NNT), defined as the number of patients who must be treated to prevent one additional adverse outcome.

Secondary outcome measures will be approached similarly to the primary outcome measure. Latency duration will be evaluated by Kaplan-Meier estimators and compared between the two treatment groups with the Log rank test and Cox proportional hazards regression, adjusted for gestational age at PPROM, if the proportional risks hypothesis is verified.

As a secondary analysis, we will analyze a per-protocol population, namely, women who received the full experimental treatment (eight tablets of nifedipine or placebo).

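### Latency curves start at PPROM although women enter at randomization, so both arms' curves are shifted upward and the early contrast is flattened; the treatment comparison itself is not biased (minor)

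*Protocol article*

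**What the plan says.** In the protocol article, Secondary outcome measures gives the first criterion for prolongation of gestation as "Latency duration, defined as the interval from PPROM to delivery". The Background uses the same clinical definition ("defined as the time elapsed from PPROM to delivery"). The two criteria that follow are counted from a different point, for example "Pregnancy prolongation beyond 48 h after randomization".

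Under Statistical analysis, "Latency duration will be evaluated by Kaplan-Meier estimators and compared between the two treatment groups with the Log rank test". A Cox model follows, "adjusted for gestational age at PPROM, if the proportional risks hypothesis is verified". That section mentions neither delayed entry nor a clock that starts at randomization.

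Entry to the trial comes after PPROM. The inclusion criteria require "Fetus alive at randomization". The exclusion criteria rule out "PPROM diagnosis ≥24 h after amniotic fluid leak", so the leak may precede the diagnosis by just under a day. For transfers, Recruitment adds: "Women transferred from another center will be eligible if PPROM occurred within the previous 24 h". The article states no general limit from diagnosis to randomization. The 48-hour study treatment begins after randomization.

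**The concern.** A woman who delivers between PPROM and randomization never enters the trial. For every woman who does enter, that interval therefore contains no delivery. If the clock starts at PPROM and everyone is counted as at risk from time zero, this guaranteed time is treated as observed survival: left truncation without delayed entry.

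Two things follow for the plotted curves. Early delivery looks rarer in both arms than it was after entry. And at any given clock time, women are at different points of the 48-hour treatment: with a gap of up to 24 h, hour 48 on the PPROM clock falls anywhere from 24 to 48 h after randomization. A short-acting tocolytic should separate the arms early, and that is the part of the curve that is flattened. The curve's value at 48 h will also differ from the trial's own outcome of prolongation beyond 48 h after randomization, which a reader may expect it to match. Prolongation of gestation is the first secondary objective listed under Trial aims.

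**Working it through.** The article states no expected latency, effect on latency or power for latency, so there is no figure of its own to reproduce. The size has to be shown under assumptions.

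**Inputs from the article.** 50 to 60% of women deliver within a week of PPROM (Background); 48-hour treatment; 351 women per arm before inflation and 850 in total (both set for the primary outcome).

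**Assumptions.** Time from PPROM to delivery is Weibull with shape 0.7 and 55% delivered by day 7. The hazard ratio is 0.6 for the 48 h after randomization and 1 afterwards. The gap from PPROM to randomization is uniform over 2 to 24 h, or 2 to 48 h because no overall limit is stated. There is no censoring.

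**Formula.** The cumulative hazard in days is H(t) = λt^0.7, with λ = −ln(0.45)/7^0.7 = 0.2045. For a control woman randomized at g days (g below 2):
- delivered within 48 h of randomization: 1 − exp{−[H(g+2) − H(g)]}
- delivered within 48 h of PPROM, given entry at g: 1 − exp{−[H(2) − H(g)]}

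In the treated arm the bracket is multiplied by 0.6.

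**One gap by hand, g = 0.5 day.** H(0.5) = 0.1259, H(2) = 0.3322, H(2.5) = 0.3884.
- From randomization: control 1 − exp(−0.2625) = 23.1%; treated 1 − exp(−0.1575) = 14.6%; difference 8.5 points.
- From PPROM: control 1 − exp(−0.2063) = 18.6%; treated 1 − exp(−0.1238) = 11.6%; difference 7.0 points.

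**Averaged over the gap.**

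| Gap | Control delivered by 48 h, from randomization | Same, PPROM clock | 48-h difference, from randomization | Same, PPROM clock |
|---|---|---|---|---|
| 2–24 h | 23% | 18% | about 8 points | about 7 points |
| 2–48 h | 21% | 12% | about 8 points | about 4.5 points |

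For the 2–24 h gap, the control median reads 7.3 days on the PPROM clock and 6.8 days from randomization.

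**The planned test, 2–24 h gap, 351 per arm, simulated.** Whole-interval log-rank power is 26% on the PPROM clock and 25% from randomization. The estimated hazard ratio is 0.91 on both. Type I error is about 5% on both.

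**A second model as a check.** Here there are 850 women, post-randomization time is Weibull with shape 0.75 and a control median of 6 days, and the hazard ratio pattern is the same.
- Undelivered at 48 h from randomization: 73.8% (control) and 83.3% (treated), a difference of 9.5 points.
- PPROM clock, 0–24 h gap: 78.4% and 86.4%, a difference of 8.0 points.
- PPROM clock, 0–48 h gap: 84.3% and 90.2%, a difference of 5.9 points.
- Log-rank power is about 0.35 and the hazard ratio 0.90 with either origin. With a constant hazard ratio of 0.8, power is about 0.90 with either origin.

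**The case against.** The strongest reply is that nothing the plan tests is damaged. The gap arises before allocation and is balanced in expectation, and the figures above show the same power, hazard ratio and type I error on both clocks. This stands.

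Next, PPROM-to-delivery is the usual clinical meaning of latency: the Background defines it so, and Table 1 lists an earlier trial with that interval as its primary outcome. Women are followed beyond delivery, so censoring should be slight, and the Kaplan-Meier curve is then simply the distribution of PPROM-to-delivery time among the women randomized. As a description of those women it is correct. This also stands, and is why the figure should be kept. It does not make PPROM the better origin for comparing treatments that start at randomization.

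Third, the 48-hour and 1-week outcomes already give an early comparison counted from randomization. That is true, and it limits the harm to the latency curves. Listing criteria with different origins is not a contradiction either, since the article says that prolongation is judged in several ways.

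Last, the analysis plan is not shown and may specify delayed entry. If it does, the concern about time at risk falls away, but the origin itself is fixed in the article.

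Three stronger readings are tempting, and the documents support none of them. A reader might infer one opening period in which no randomized woman could deliver; the event-free interval is each woman's own, and a woman randomized 2 h after PPROM can deliver at hour 3. A reader might infer bias between the arms; a gap that precedes randomization does not produce it. A reader might infer a loss of power from a log-rank test cut off at 48 h; under the first model that test has 71% power on the PPROM clock against 82% from randomization, but the article plans no such test.

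**Conclusion.** The point holds as a minor one about the level and time scale of the latency curves. With PPROM as time zero and no delayed entry, both curves lie too high as a picture of what happens after entry, and the visible 48-hour contrast falls from about 8 to about 7 points (2–24 h gap) or to about 4.5 points (2–48 h gap). These sizes rest on the assumed Weibull shape, the assumed early hazard ratio and the assumed gap, none of which the article gives. The direction needs only that women enter after PPROM and still pregnant, which it does state. The primary outcome, the sample size, the planned log-rank and Cox comparison, and the 48-hour and 1-week outcomes are not affected.

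**What to change.** Define the time-to-event outcome as randomization to delivery, and run the Kaplan-Meier, log-rank and Cox analyses on it. The adjustment for gestational age at PPROM can stay. Keep PPROM-to-delivery as a descriptive figure by arm, for comparison with the literature. If curves on the PPROM clock are shown, let each woman enter the risk set at her randomization time; the risk sets will be small in the first hours, so the start of such a curve will be unstable, and it still will not line up with the treatment window.

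The cost is one line in the outcome definition and a change of origin in the analysis code. Randomization runs through a web-based system, so its time should already be on record. No further patients or data are needed.
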